### Randomisation, allocation, and blinding

A permuted block randomisation sequence (block sizes of four), stratified by clinical condition, was generated using Stata 13 by the study biostatistician (EC) prior to trial commencement. The randomisation sequence is stored in a password-protected file not accessible to the researcher responsible for enrolling and assessing participants. Treatment allocation remains concealed until immediately before a participant’s first assessment, at which time the assessing researcher is informed of the allocation by the study administrator. Due to the nature of the intervention, both the participant and assessing researcher are not blinded to group assignment. During primary data analysis, the biostatistician will be blinded to treatment group (i.e. by using unlabelled numerical coding for the treatment group variable within the dataset, recoverable by the study administrator).

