**Methods/design:**

We are undertaking a two-group, parallel, randomised controlled trial (RCT) comparing the effects of a personalised relaxation intervention on sleep quality, daytime symptoms, and functioning in patients with CFS (*n* = 64) and MDD (*n* = 64). Following identification of the method that best enhances autonomic responding (such as heart rate variability), participants randomised to the active intervention will practise their recommended method nightly for 4 weeks. All participants will keep a sleep diary and monitor symptoms during the trial period, and they will complete two face-to-face assessments, one at baseline and one at 4 weeks, and a further online assessment to evaluate lasting effects of the intervention at 2 months. Assessments include self-report measures of sleep, wellbeing, and function and monitoring of autonomic responses at rest, in response to the relaxation method and during nocturnal sleep. Treatment outcomes will be analysed using linear mixed modelling.

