### Sampling and recruitment

Potential participants are screened by email or telephone to ensure they meet eligibility criteria before proceeding to enrolment. Individuals are eligible to participate if they are aged between 18 and 65 years at the time of assessment; have been diagnosed by a physician or psychiatrist to meet international diagnostic criteria for CFS [1] or MDD with fatigue as a significant feature as defined by Diagnostic and Statistical Manual of Mental Disorders, 5^th^ edition (DSM-V) diagnostic criteria [44]; have self-reported normal hearing; sufficient English language proficiency to complete questionnaires and understand instructions; and a willingness to participate and comply with the longitudinal nature of the study. Individuals who are concurrently engaged in relaxation or mindfulness-based therapies; are pregnant; have other significant illnesses or major diagnoses such as primary sleep disorder, heart conditions, uncontrolled diabetes, chronic infections, or psychotic disorders; or who take regular medications that affect autonomic activity, including beta blockers and anti-hypertensives, are excluded from the study. Use of anti-depressant medication or hormonal contraception is recorded, but is not exclusionary.

Patients with CFS are recruited from an academic tertiary referral clinic which specialises in the management of chronic fatigue states (UNSW Fatigue Clinic in Sydney, Australia) via advertisements placed in clinic waiting rooms and targeted email advertisement distribution to the clinic’s opt-in volunteer research register. Participants with MDD are recruited from the Black Dog Institute (BDI), a mental health research centre and clinic in Sydney, via online advertisements and email distribution to the BDI volunteer research register.

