### Sample size estimates

Statistical power and appropriate effect size estimates are based on published recommendations [45] and unpublished pilot data using this protocol collected by our group. A sample size of 128 participants (64 in each treatment arm) provides ≥ 80% power (with a Bonferroni-adjusted significance level of 0.013 allowing for multiple comparisons) to detect improvements of approximately 1 standard deviation in sleep quality (2-point reduction), fatigue (3-point reduction), and functioning (8-point improvement) measures in the intervention arm [46]. This conservative estimate will allow for an attrition rate of up to 10%.

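### Fixed blocks of four within each condition, with one unblinded researcher who enrols and assesses, leave avoidable predictability: up to a third of allocations can be deduced if the block size is known

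*Protocol article*

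**What the plan says.** The section Randomisation, allocation, and blinding describes "A permuted block randomisation sequence (block sizes of four), stratified by clinical condition", generated by the study biostatistician before the trial began. No other block size is named and no random variation of size is described. The sequence is "stored in a password-protected file not accessible to the researcher responsible for enrolling and assessing participants". The study administrator tells the assessing researcher each participant's allocation just before that participant's first assessment. The same section states that "both the participant and assessing researcher are not blinded to group assignment".

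Under Sampling and recruitment, "Potential participants are screened by email or telephone to ensure they meet eligibility criteria before proceeding to enrolment". The article does not say who does the screening.

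The planned total is 128, with 64 per treatment arm (Sample size estimates) and 64 per condition (Abstract, Methods/design). Trial status reports that recruitment began in April 2017 and is to run for two years or until the sample is reached.

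**The concern.** A password hides the list but not the pattern. The person who enrols also learns every earlier allocation in each of the two strata. With a single fixed block size, those past allocations can reveal the next one: after two like allocations at the start of a block the other two are settled, and the fourth is always settled.

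If the next allocation can be foreseen, it can influence who is enrolled next, even without any intent to bias. Most eligibility criteria are specific, but some need judgement: willingness to comply with a longitudinal study, adequate English, and fatigue as a significant feature of the depression.

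This trial is exposed to such an influence because it is open, compares an active intervention with monitoring alone, and has self-reported primary outcomes (Outcomes). The Data analysis plan adjusts for the baseline value of the outcome. That helps with measured differences but not with unmeasured ones such as motivation. Baseline values are also collected at the first assessment, after the allocation has been released to the researcher.

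**Working it through.** The article gives no figure for predictability, so there is none to reproduce.

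**Inputs**
- Block size 4, two strata: Randomisation, allocation, and blinding.
- 1:1 allocation (64 per arm of 128), so two of each arm per block: Sample size estimates.
- 64 per condition, so 64/4 = 16 blocks per stratum and 32 in all: Abstract.
- Assumption, not stated in the article: the researcher knows the block size and tracks each stratum.

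**Share deducible with no one pending.** The six equally likely blocks are AABB, ABAB, ABBA, BAAB, BABA and BBAA.
- The fourth allocation is determined in 6 of 6 blocks.
- The third is determined in 2 of 6 (AABB, BBAA).
- Share known with certainty: (6 + 2)/(6 × 4) = 8/24 = 33.3%.
- Expected number: 64/3 = 21.3 per condition and 128/3 = 42.7 overall. The possible range is 32 to 64, since each of the 32 blocks yields one or two. The standard deviation is √(32 × 1/3 × 2/3) = 2.7.

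**Best-guess rate with no one pending.** The chance of a correct guess at positions 1 to 4 is 1/2, 2/3, 2/3 and 1. The mean is (0.5 + 0.667 + 0.667 + 1)/4 = 70.8%, against 50% under simple randomisation.

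**Effect of a queue.** Allocation is released only at the first assessment, so an earlier participant in the stratum may be enrolled but not yet revealed.
- One pending: only the fourth position can be determined, and only if the first two are alike. The share is 2/24 = 8.3%; the best guess is (0.5 + 0.5 + 0.667 + 0.667)/4 = 58.3%.
- Two pending: nothing is certain (0%); the best guess is (0.5 + 0.5 + 0.5 + 0.667)/4 = 54.2%.

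**How often the queue might be empty (illustration only).** The interval from enrolment to first assessment is not given. At 64 per stratum over about 104 weeks, enrolment is about 0.6 per week. If arrivals are Poisson, a one-week interval gives about 0.54 × 33.3% + 0.33 × 8.3% ≈ 21% deducible. A two-week interval gives about 0.29 × 33.3% + 0.36 × 8.3% ≈ 13%.

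**Randomly mixed block sizes.** These were simulated with 64 per stratum, 3,000 runs, no one pending, and an observer who knows the set of sizes but not their order.

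| Block sizes | Known with certainty | Best guess right |
|---|---|---|
| 4 only | 33.3% | 70.8% |
| 4, 6 | 5.6% | 69.1% |
| 2, 4, 6 | 4.1% | 70.2% |
| 4, 6, 8 | 2.2% | 67.8% |

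**The case against.** The strongest reply is that a genuine concealment mechanism is in place. The list was made in advance by the biostatistician, is closed to the enrolling researcher, and is released one case at a time by a different role. A reader might infer from the fixed blocks that concealment fails, or that a third of allocations are in fact known in advance. The article supports neither. It does not say that the researcher knows the block size, and a full protocol might record that it was withheld. Printing the size during recruitment makes such knowledge plausible but does not show it. A short queue also reduces the deducible share sharply. This part of the reply stands, and one third is the figure under full knowledge with an empty queue.

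Other limits also stand:
- Not every outcome is self-reported; change in heart rate variability is a secondary outcome.
- Recruitment draws on two sources, a fatigue clinic and a mental health institute; only the assessments share one site.
- The article does not describe how appointments are ordered, so no claim can rest on that.
- Diagnosis is made by a physician or psychiatrist and most exclusions are specific, so discretion is limited.
- Mixed blocks lower the best-guess rate only slightly.

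The reply does not remove the point that the one stated block size is fixed and small, and that the role which enrols sees every past allocation.

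**Conclusion.** The concern holds in a conditional form. As written, the plan withholds the list properly but leaves predictability that could easily be avoided. If the enrolling researcher knows the block size and tracks each stratum, 33.3% of allocations (about 43 of 128) can be deduced when no one is pending, 8.3% with one pending and none with two. The best-guess rates are 70.8%, 58.3% and 54.2%. The article does not give the length of the queue, so the realised share cannot be fixed more closely. The whole-trial figure also includes participants already allocated.

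Nothing in the article shows that any allocation was foreseen or that enrolment was influenced. The point is worth acting on because the trial is open, its primary outcomes are self-reported, and the remedy is cheap.

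**What to change.** For the remaining allocations:
- Complete any open block in each condition. The biostatistician then generates a new list within each condition with randomly mixed block sizes, for example 4, 6 and 8.
- Keep the sizes and the mix from the enrolling researcher, and do not publish them while recruitment continues.
- Report baseline balance between arms separately for participants allocated before and after the switch.

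Under the working's assumptions, certain knowledge falls from 33.3% to about 2%, while the best-guess rate falls only from 71% to about 68%. Requiring eligibility and consent to be final before each release would add little, because prediction from earlier allocations acts before that step.

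The cost is one new list, a short amendment and a possible end-of-trial imbalance of a few participants per stratum. Allocations already made are not helped. The number remaining is not stated, so the benefit cannot be expressed as a count of participants.

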### Data collection

All consenting participants complete two face-to-face assessments, 4 weeks apart, and a further set of questionnaires completed online 8 weeks after the initial assessment (Fig 2). At the first assessment (lasting approximately 90 min), participants’ demographic, health, and symptom information are documented. Autonomic activity at rest and in response to each of the relaxation methods (see below) is recorded. Results from this initial testing determine which method participants randomised to the intervention group will practise daily during the 4-week intervention (i.e. the method which induced the greatest increase in HRV for that participant). Before leaving, all participants are fitted with a non-invasive ambulatory bioharness (Equivital EQ-02, Hidalgo Ltd., Cambridgeshire, UK) for 24-h monitoring and issued a sleep/activity/symptom log to complete over the next 4 weeks (see subsequent paragraphs). The second assessment lasts approximately 45 min and consists of a briefer version of the initial assessments (i.e. assessment of health, symptoms, and autonomic activity). Those in the control arm will be offered the personalised intervention at this assessment. The third assessment consists of online self-report measures, including questionnaires about the participant’s sleep, symptoms, and current frequency of relaxation practice. This will allow us to assess possible enduring benefits of the intervention in the active group, and to determine whether subjective improvements are evident in the monitoring group who will have practised their assigned intervention for 4 weeks. Participants will be emailed a personalised link to the online questionnaire. An automated reminder email will be sent after 1 week and again after 2 weeks, if the participant has not completed the questionnaire. The online nature of this assessment will reduce inconvenience for the participants and hence minimise attrition.

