The personality traits neuroticism and extroversion are quantified using the two subscales of the Eysenck Personality Questionnaire Short form (EPQ-SF) [52]. Each of these subscales consists of 12 questions that require a ’yes’ or ’no’ answer. The total score for each subscale is 12, with a higher score indicating higher trait attributes. Cronbach’s alpha values for males and females are 0.84 and 0.80 respectively for the neuroticism scale, and 0.88 and 0.84 respectively for the extroversion scale. Physical activity is documented using the International Physical Activity Questionnaire (IPAQ) Short Form [53]. The questionnaire consists of four questions on time spent in walking, vigorous and moderate-intensity activity, and sedentary activity, where vigorous activities include heavy lifting or fast bicycling, and examples of moderate activities are carrying light loads or bicycling at a regular pace. For each of these activity types the average time usually spent on each is recorded for ‘the last 7 days’, and total scores are calculated with consideration of the energy expenditure for each activity category. Spearman correlation coefficients, reported to indicate test-retest reliability, were at an acceptable level, with 75% of the correlation coefficients observed above 0.65 [53].

The Medical Outcomes Survey Short Form-36 (MOS SF-36) is a 36-item questionnaire used to measure aspects of health and functional disability across eight domains including physical functioning, role limitations due to physical health, role limitations due to emotional problems, energy/fatigue, emotional wellbeing, social functioning, pain, and general health. Eight scaled scores are derived, which are the weighted sums of the questions in their domain. Each score is directly transformed into a 0–100 scale on the assumption that each question carries equal weight. A lower score indicates more disability/less health. Internal consistency reliability estimates of the eight scales are reported to range between 0.73 to 0.96, with a median of 0.95; median estimates for test-retest reliability were 76 [54]. All participants are asked to complete these questionnaires at all assessments, including baseline and follow-up at 4 weeks and for the online assessment. The EPQ-SF is only administered at the baseline assessment.

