After the presentation of each relaxation method, participants are asked how relaxing they found the method (on a scale ranging from ‘not at all’ to ‘very’ relaxing) and whether they would expect the intervention to be helpful in reducing their symptoms (‘no’, ‘maybe’, ‘yes’). At the second assessment, participants in the intervention group are asked if they were satisfied with the intervention in improving their symptoms (on a scale ranging from ‘not at all’ to ‘completely’). At the 8-week online assessment, participants are asked if they have continued to practise their assigned relaxation method, and if so, how frequently.

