### Data analysis plan

The outcome variable (change scores) will be analysed using linear mixed modelling. Treatment arm (intervention/control) and clinical condition (MDD/CFS) will be included in models as a dichotomous between-subjects variable. Baseline values of the outcome variable will also be included as a covariate (to control for chance differences between treatment arms at baseline). Bivariate associations between demographic measures and outcome variables will be explored using Pearson pairwise correlations. The outcome of these analyses will inform about additional variables to be included in multivariate models as covariates.

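### Allocation is released to the assessor before the baseline assessment, so the baseline values used in the change scores and as covariate are not protected from knowledge of the arm

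*Protocol article*

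**What the plan says.** All references are to the protocol article.

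- **Timing of disclosure** (Randomisation, allocation, and blinding): "Treatment allocation remains concealed until immediately before a participant’s first assessment, at which time the assessing researcher is informed of the allocation". The study administrator passes on the allocation.
- **Blinding** (same section): because of the kind of intervention, "both the participant and assessing researcher are not blinded to group assignment". Only the biostatistician is blinded, during the primary analysis.
- **Concealment up to that point** (same section): the sequence is "stored in a password-protected file not accessible to the researcher responsible for enrolling and assessing participants".
- **Content of the first assessment** (Data collection): "participants’ demographic, health, and symptom information are documented", and "Autonomic activity at rest and in response to each of the relaxation methods (see below) is recorded".
- **Questionnaires** (Self-report measures): "All participants are asked to complete these questionnaires at all assessments, including baseline and follow-up at 4 weeks and for the online assessment". After each relaxation method, participants also rate "whether they would expect the intervention to be helpful in reducing their symptoms".
- **Same baseline in both arms** (Sleep and symptom monitoring): control participants undergo the baseline and 4-week assessments that the intervention group undergoes. They are told that four weeks of monitoring come before they receive a method. The article does not say when they are told.
- **Use of baseline** (Outcomes; Data analysis plan): the primary outcomes are changes in self-reported sleep quality, symptoms and functioning, modelled as change scores. "Baseline values of the outcome variable will also be included as a covariate", with the stated purpose of handling chance imbalance between arms.

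**The concern.** The stated order is disclosure first, baseline second. A baseline recorded after the arm is known is no longer guaranteed to be independent of treatment. It can differ between arms for a reason other than chance, and chance imbalance is all the covariate is meant to correct.

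The baseline enters the analysis twice: it is subtracted to form the change score, and it is adjusted for. A shift in one arm's recorded baseline therefore passes into the estimated effect on every self-reported primary outcome. The expectancy ratings, resting HRV and three-method recordings come from the same session, run by someone who knows the arm.

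The kind of intervention explains why follow-up must be open-label. It does not explain an open-label baseline, because every participant goes through the same baseline procedures and the method is chosen only once the recordings are finished (Autonomic assessment). At stake is an avoidable bias that later analysis cannot fully repair.

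**Working it through.** **1. Order of events.** Disclosure comes immediately before the first assessment. The first assessment supplies the baseline questionnaires, expectancy ratings, resting HRV and method-selection HRV. The primary outcome is the change from those questionnaires, adjusted for them. The assessor's knowledge at baseline is explicit. The participant's is not: the article says participants are not blinded but gives no time at which they learn their arm.

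**2. Is the arm needed during the baseline measures?** Both arms have the same baseline assessment. The method is selected from the recordings afterwards, and controls are offered a personalised method at week 4. No stated step before method selection depends on the arm.

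**3. How a baseline shift enters the effect.** Let T = 1 for active and 0 for control, Y0 the true baseline and Y1 the 4-week score, both in SD units with correlation rho. Let the recorded baseline be O = Y0 + b·T, with follow-up unaffected and no true effect.

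- Change without adjustment: E(Y1 − O) differs between arms by −b.
- Change adjusted for O (the planned model): the arm coefficient is −rho × b.

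Adjustment therefore shrinks the bias from b to rho × b but does not remove it.

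**4. Size, as illustration.** Inputs from the article (Sample size estimates): 64 per arm; alpha 0.013, taken as two-sided because sidedness is not stated; a 2-point sleep-quality change is about 1 SD, so SD is about 2 points. Assumptions not in the article: b = 0.1 to 0.3 SD and rho = 0.3 to 0.7.

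SE = √[(1 − rho²) × 2/64]. Critical value for 0.013 two-sided: 2.484. Rejection rate = Φ(−2.484 + bias/SE) + Φ(−2.484 − bias/SE).

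| rho | b | Bias (SD) | Sleep-quality points | SE | Rejection rate |
|---|---|---|---|---|---|
| 0.3 | 0.1 | 0.03 | 0.06 | 0.169 | 1.4% |
| 0.3 | 0.3 | 0.09 | 0.18 | 0.169 | 2.7% |
| 0.5 | 0.1 | 0.05 | 0.10 | 0.153 | 1.8% |
| 0.5 | 0.2 | 0.10 | 0.20 | 0.153 | 3.4% |
| 0.5 | 0.3 | 0.15 | 0.30 | 0.153 | 6.7% |
| 0.7 | 0.1 | 0.07 | 0.14 | 0.126 | 2.8% |
| 0.7 | 0.3 | 0.21 | 0.42 | 0.126 | 20.6% |

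A simulation of 4,000 trials at rho 0.5 and b 0.2 gave a bias of 0.10 SD and a rejection rate of 3.2%, in line with the formula.

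**5. Direction.** Nearly all the excess falls in one tail. At rho 0.5 and b 0.2, bias/SE = 0.10/0.153 = 0.653, so the two tails are Φ(−1.831) = 3.4% and Φ(−3.137) = 0.1%. Which tail depends on the sign of b. On a score where higher is worse:

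- If hope makes the active arm rate itself better at baseline, b is negative and the bias is +rho × |b|: the intervention looks worse.
- Disappointed controls rating themselves worse has the same effect.
- If the active arm overstates its symptoms at baseline, the bias favours the intervention.

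**6. If the shift persists to week 4.** With the same shift s at both times, the adjusted bias is s − rho × s = (1 − rho)s. For s = 0.2 this is 0.10 (rho 0.5) or 0.06 (rho 0.7). A clean baseline with a shifted follow-up gives the full 0.20.

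**The case against.** Several points on the other side have weight.

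- **Participant knowledge.** The primary outcomes are self-completed, so the most natural mechanism needs the participant to know the arm. The article names only the assessor as informed at that point. A reader might infer that participants demonstrably complete the baseline knowing their arm. The text makes that possible, not certain. This stands.
- **Direction.** A reader might also infer that the design inflates false claims of benefit. The documents do not support that. The most obvious reactions, hope in the active arm and disappointment in controls, would hide benefit if follow-up is unaffected. This stands: the rejection rates above are two-sided and must not be read as false-benefit rates.
- **Persistence.** If the same reporting tendency lasts to week 4, a shifted baseline partly offsets a shifted follow-up, and a clean baseline need not lower the total bias (step 6). The arithmetic is right and limits the promised gain. Still, relying on two unmeasured biases to cancel is no reason to keep an unprotected baseline.
- **Size.** No figure in the article supports a shift of 0.1 to 0.3 SD. At the low end the rejection rate barely moves from 1.3%, and the planned effect is about 1 SD. This stands.
- **HRV.** It is a secondary outcome, processed with a software module, and the method is chosen by a stated rule (largest increase). The HRV concern is the weaker part.
- **Concealment.** The sequence is withheld from the researcher who enrols and assesses. Reading this point as a failure of allocation concealment at enrolment would be wrong.
- **Mid-trial change.** Recruitment began in April 2017 (Trial status), so a change now splits the cohort into two procedures. This is a real cost, but a small one.

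**Conclusion.** The point holds in a limited form. It is certain that the assessor knows the arm while the baseline is collected, and that this baseline supplies both the change score and the covariate. It is possible, but not stated, that participants know it as well. An allocation-driven shift b in one arm's baseline biases the adjusted effect by about rho × b when follow-up is unaffected. Under the assumed ranges that is 0.03 to 0.21 SD, or 0.06 to 0.42 sleep-quality points. The documents determine neither the size nor the sign of b.

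The weakness is avoidable because nothing in the stated procedures requires the arm before the baseline measures are finished. It is a moderate, direction-uncertain weakness with a cheap remedy. It does not show that the trial's result will be biased towards benefit.

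**What to change.** In Randomisation, allocation, and blinding, change the disclosure rule. The study administrator should release the allocation to assessor and participant only once consent, the baseline questionnaires, the expectancy ratings, the resting and three-method recordings and the method selection are complete. This happens at the same visit and applies to all remaining participants.

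For participants already enrolled:

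- Report when they learned their arm.
- Add a sensitivity analysis of the 4-week scores themselves (not change scores) by arm and clinical condition, without the baseline covariate. A shifted baseline cannot affect this estimate. It does not address open-label reporting at week 4, and it is less precise: SE = √(2/64) = 0.177 SD, against 0.153 at rho 0.5 or 0.126 at rho 0.7.

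Cost: a short procedural amendment that moves one step within an existing visit, with no additional visit. The cohort will contain participants assessed under two procedures, which the report should state. The 24-hour harness and the daily log start after these steps and remain open-label either way.

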#### Autonomic assessment

Laboratory-based autonomic measures include three-lead electrocardiogram (ECG) and respiration (via a strain gauge transducer) recorded at 1 kHz using PowerLab and LabChart Pro 8 (ADInstruments, Bella Vista, Australia). To obtain a baseline assessment of cardiac autonomic functioning, participants are asked to relax in a semi-reclined position for 10 min, in silence. Autonomic responses are also measured during the presentation of each of the three relaxation methods (each ~ 10-min duration). Immediately after the assessment, data are processed and analysed using the LabChart HRV 2.0 module to determine the participant’s baseline HRV and his/her response during each of the relaxation methods to allow selection of the method that induced the largest increase in HRV response for that participant.

Continuous 24-h monitoring of autonomic activity (including during nocturnal sleep) is achieved via a lightweight bioharness system (Equivital, Hidalgo) at baseline and at 4 weeks. Participants are fitted with a non-invasive chest harness consisting of a two-channel ECG (sampling rate 256 Hz), respiratory belt (25.6 Hz), skin temperature sensor (25.6 Hz), and tri-axial accelerometer (25.6 Hz, enabling detection of body orientation and movement). The overnight data are extracted and processed using LabChart Pro.

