### Outcomes

The primary outcomes for this study are changes in self-reported sleep quality, symptoms, and functioning. These will be assessed by self-report measures at the 4-week assessment. Secondary outcomes are changes in HRV and interventional acceptability.

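### Blinding is described only for the biostatistician; no masked processing is provided for the HRV recordings, the one named outcome not based on self-report

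*Protocol article*

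**What the plan says.** The section Randomisation, allocation, and blinding of the protocol article gives the blinding scheme in three parts:

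- Timing: "Treatment allocation remains concealed until immediately before a participant’s first assessment, at which time the assessing researcher is informed of the allocation".
- Who is not blinded, with the nature of the intervention given as the reason: "both the participant and assessing researcher are not blinded to group assignment".
- Who is blinded: "During primary data analysis, the biostatistician will be blinded to treatment group", by means of an unlabelled numerical arm code that the study administrator can decode.

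The Outcomes section states that "The primary outcomes for this study are changes in self-reported sleep quality, symptoms, and functioning" and that "Secondary outcomes are changes in HRV and interventional acceptability". Acceptability is a participant rating: under Self-report measures, "participants in the intervention group are asked if they were satisfied with the intervention in improving their symptoms".

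On HRV processing, the section Autonomic assessment says of the laboratory recordings: "Immediately after the assessment, data are processed and analysed using the LabChart HRV 2.0 module". The purpose given in the same sentence is to choose the relaxation method. Of the 24-hour ambulatory recordings it says: "The overnight data are extracted and processed using LabChart Pro". Neither sentence names an operator or mentions masking.

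**The concern.** All primary outcomes are rated by participants who know their arm, and the comparator is symptom monitoring with the intervention to follow. Expectation can therefore act on every primary result. HRV is the one named outcome that does not pass through the participant's own rating. It also carries the part of the first aim that concerns autonomic balance, and the abstract's claim to shed light on mechanism.

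An HRV value is not fixed when the recording is made. Someone or something has to deal with artefact and ectopic beats, choose the segment analysed and, for a 24-hour record, decide which part is sleep. If any of these steps involves judgement by a person who knows the arm, the difference between arms can be shifted before the dataset exists. A biostatistician who then sees only arm codes cannot remove that shift. The reason given for leaving people unblinded does not apply to this step.

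**Working it through.** The plan states no figure on this point, so the check is mainly a reading of its statements side by side.

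**1. Which outcomes are not self-report?** The primary outcomes (sleep quality, symptoms, functioning) are self-reported. Of the two secondary outcomes, acceptability is a participant rating and HRV is a physiological recording. HRV is therefore the only named outcome not based on self-report.

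**2. Who knows the arm, and when?** The assessor is told just before the first assessment, so the baseline recording is already made with the arm known. Baseline values enter the model as a covariate (Data analysis plan), so both ends of the HRV change are recorded unblinded.

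**3. Does the stated reason cover HRV processing?** A participant cannot be blinded to practising relaxation, and neither can the person running the visit. A stored ECG file can be processed without knowing either the arm or the visit. The reason does not reach this step.

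**4. Does the biostatistician's blinding cover it?** No. It starts with the dataset, in which the HRV values are already fixed.

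**5. Do the study identification numbers cover it?** Not by themselves. Ethics and dissemination says one number per participant is used on all materials, including computer files. Anyone who was told a participant's allocation can link the number to the arm. The numbers do show that masked processing is feasible.

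**6. Who processes the files?**

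| Recording | Stated operator | What can be inferred |
|---|---|---|
| First-visit laboratory | none | The result decides the assigned method and is processed straight after the assessment, so processing by the unblinded assessor is a fair inference |
| Week-4 laboratory | none | Nothing stated |
| Overnight, both times | none | Nothing stated |

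**7. How much could it matter?** The documents give no reading error, so this is an illustration only. Assume that arm-dependent processing shifts HRV by b standard deviations, that there is no true effect, and that 64 per arm (Sample size estimates) are compared by a two-sided test at 5%, normal approximation.

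Standard error of the difference in SD units: √(2/64) = 0.177.

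False-positive rate: 1 − Φ(1.96 − b/0.177) + Φ(−1.96 − b/0.177).

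- b = 0.1: 8.7%
- b = 0.2: 20.5%
- b = 0.3: 39.6%

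With b = 0 the rate is 5%. Nothing in the documents makes any of these values of b more plausible than zero.

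**The case against.** A reader might infer that the plan has the unblinded assessor process the HRV outcome recordings, so that this outcome is shown to be biased. The documents do not support that. Both processing sentences are passive and name nobody. The sentence about immediate processing concerns the choice of method at the first visit, and nothing says that those values are reused as outcome data or that week-4 files are handled in the same way.

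Further points on the other side:

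- Processing is by software, and no manual editing is described. The room for judgement may be small.
- The ambulatory harness includes an accelerometer and participants keep a daily sleep log, so an objective sleep window could be set.
- A condensed article may leave the operator and the artefact rules to a fuller document.
- HRV is secondary. Masked processing would also not blind the participant during the recording, so it cannot make HRV free of every effect of unblinding.

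Most of this stands, and it limits the claim: no actual bias is shown, and no size can be given. It does not remove the point. The article sets out a blinding scheme with a reason, and that scheme stops at the dataset although the reason does not extend to processing stored files. The absence of artefact rules from an article would not be a finding by itself. The place where the described blinding begins is a design choice that can be improved.

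**Conclusion.** The concern holds in a limited form. As described, blinding applies only to the biostatistician at the dataset stage, and no masked processing is provided for the only named outcome that is not self-report. The stated reason for not blinding does not justify that gap.

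The size of any bias is unknown. The shifts of 0.1 to 0.3 SD used above are assumptions that show sensitivity; they are not estimates. The primary outcomes and the sample size are untouched. What is at stake is how far the HRV result can be trusted as support for the autonomic aim and the mechanism claim.

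The conclusion assumes that processing leaves some room for judgement and that masking is not already in place. If the outcome files are already processed masked, a sentence saying so in the blinding section settles the point.

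**What to change.** Keep the immediate processing at the first visit, and use it only to select the relaxation method.

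For the HRV outcome:

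1. The study administrator, who can already decode the arm variable, re-codes the baseline and week-4 laboratory resting files and the overnight files so that arm, participant identification number and visit are hidden.
2. Existing staff process these files in one batch, before any unmasking, with detection and artefact settings fixed in advance.
3. The sleep window is set by a fixed rule, for example from the sleep log and accelerometer data already collected.
4. The section Randomisation, allocation, and blinding states that extraction of the HRV outcome is masked to arm and visit.

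The cost is file renaming and re-running software already in use. The one downside is that baseline laboratory files are processed twice. The change can still be made after recruitment has begun, because it works on stored recordings and the article commits to keeping all data for at least 15 years.
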